### Staging and impact on patient management

Tentative staging based on FAPI and [^18^F]FDG PET/CT data will be performed according to the International Federation of Gynecological Oncology’s classification system (FIGO) and the American Joint Committee on Cancer (AJCC 8th) edition TNM classification. Staging, as determined at the tentative MDT, will be compared for [^68^Ga]Ga-FAPI-46 PET/CT and [^18^F]FDG PET/CT, both at primary staging and post-NACT staging, and patients will be classified as “upstaged”, “unchanged”, or “downstaged” due to [^68^Ga]Ga-FAPI-46 PET/CT. The proportions of patients in these categories will be calculated. Furthermore, at the tentative MDT, the treatment strategy (e.g., operability, resectability, palliative treatment, other treatment) will be evaluated purely based on the [^68^Ga]Ga-FAPI-46 PET/CTs (replacing [^18^F]FDG PET/CTs) both at primary staging and at post-NACT staging. The proportion of patients with a hypothetically changed treatment strategy will be calculated. Supplementary imaging results (excluding the FDG PET/CT results), biochemical data, and medical records prior to the staging time point will be available for the clinicians attending the tentative MDT to mimic the situation at the clinical MDT.

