### Secondary objectives

The secondary objectives are as follows: (1) To estimate the proportion of patients hypothetically treated differently due to [^68^Ga]Ga-FAPI-46 PET/CT replacing [^18^F]FDG PET/CT; (2) to investigate the intensity of [^68^Ga]Ga-FAPI-46 uptake in tumor deposits; (3) to investigate the feasibility of FAPI PET/CT for chemotherapy-response assessment compared to FDG PET/CT; (4) to investigate the prognostic value of FAPI PET/CT compared to FDG PET/CT at primary staging and post-NACT staging; (5) to evaluate potential unexpected FAPI PET/CT findings; and (6) to evaluate the safety of [^68^Ga]Ga-FAPI-46 injections.

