**Fig. 1 Fig1:**
[figure not shown]
FAPI PET in ovarian cancer study design and flow

[^68^Ga]-Ga-FAPI-46 PET/CT data will be interpreted after enrollment of all patients and compared to the [^18^F]-FDG PET/CT data. Histopathology of the resected specimens and biopsies will serve as a reference standard for calculating the diagnostic accuracy. For suspicious lesions not confirmed by histopathology, other imaging modalities (US, MRI, CT), biochemistry, and medical records will be used for classification. The clinical impact of [^68^Ga]Ga-FAPI-46 PET/CT, both at primary staging and post-NACT staging, will be evaluated at a retrospective tentative MDT with the participation of an onco-gynecological surgeon, an oncologist, a pathologist, and a nuclear medicine physician, all of which specialize in the treatment of ovarian cancer. The tentative MDT will be performed retrospectively and therefore has no influence on the actual treatment of patients; moreover, the MDT differs from the clinical MDT, as clinicians will present study-related [^68^Ga]Ga-FAPI-46 PET/CTs instead of [^18^F]FDG PET/CTs. The study flow is depicted in Fig. 1.

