### Study population

#### Sample size and patients

Patients with biopsy-verified OC prior to the gynecological cancer MDT *or* highly suspected to have OC (based on all information presented at the gynecological cancer MDT) will be recruited until a total of 50 patients with histopathologically confirmed OC have been included. The upper limit of recruited patients is set at 60. Recruitment will take place at an outpatient clinic related to the Dept. of Gynecology and Obstetrics Aalborg University Hospital (Aalborg UH) by trained staff in accordance with national requirements [53]. Because an official sample size calculation is not feasible due to former study limitations, e.g., highly selected patients and lack of histopathology of metastases, the desired number of participants is based on the possibility of recruiting patients within 1.5-2 years at our institution, and more importantly, valid estimates of diagnostic accuracy are obtainable with the planned number of patients in an unselected consecutive cohort. Approximately 25 patients are estimated to undergo direct surgery after [^68^Ga]Ga-FAPI-46 PET/CT (Group A), and 25 patients will undergo NACT followed by a second [^68^Ga]Ga-FAPI-46 PET/CT (Group B). The recruitment strategy is based on unpublished clinical data from our institution and from published literature, where approximately 10–15% of the patients with highly suspected OC (based on all available information at MDT) had other non-OC malignancies or rarely benign conditions upon histopathology, e.g., endometriosis, gastric cancer (i.e., Krukenberg tumors), and colorectal cancer [24, 54].

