### Study participant eligibility

The inclusion criteria are; (1) Patients newly diagnosed with biopsy-verified OC *or* highly *s*uspected to have OC (based on all the data presented at the gynecological cancer MDT) *and* referred to primary staging with [^18^F]FDG PET/CT; (2) patients deemed resectable and operable at the MDT with or without neoadjuvant chemotherapy; (3) patients considered physically and mentally able to participate in the research project; (4) patients eighteen years or older and able to consent to participate in the project; and (5) patients can read and understand Danish. The main exclusion criteria are: (1) Patients unfit for surgery; (2) patients with recurrent OC; (3) patients with concurrent non-OC malignancies; (4) patients unable to participate in PET/CT; (5) patients with a history of hypersensitivity to [^18^F]FDG or FAPI tracers; (6) pregnant, lactating, or breastfeeding patients or fertile women not using effective contraceptives; and (7) known medical conditions that would significantly decrease the reliability of the data obtained as part of this study. A full set of exclusion criteria can be found at clinicaltrials.gov (NCT05903807) and euclinicaltrials.eu (EU CT: 2023-505938-98-00).

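### Treatment change due to FAPI is measured against an earlier decision by a different meeting, so ordinary re-decision variability is counted as FAPI impact

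*Protocol article*

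**What the plan says.** Secondary objectives, item 1, is "To estimate the proportion of patients hypothetically treated differently due to [^68^Ga]Ga-FAPI-46 PET/CT replacing [^18^F]FDG PET/CT". The wording attributes the change to the tracer.

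Study flow overview says that patients are actually treated according to a standard work-up that includes FDG PET/CT and contrast-enhanced CT. FAPI scans stay blinded and are read only once every patient has been enrolled. A tentative MDT then meets retrospectively, and "the MDT differs from the clinical MDT, as clinicians will present study-related [^68^Ga]Ga-FAPI-46 PET/CTs instead of [^18^F]FDG PET/CTs".

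Staging and impact on patient management fixes what that meeting sees. There, "the treatment strategy (e.g., operability, resectability, palliative treatment, other treatment) will be evaluated purely based on the [^68^Ga]Ga-FAPI-46 PET/CTs (replacing [^18^F]FDG PET/CTs", and this applies at primary staging and again after NACT. As to other material, "Supplementary imaging results (excluding the FDG PET/CT results), biochemical data, and medical records prior to the staging time point will be available", the stated aim being to imitate the clinical MDT. The endpoint is the simple proportion of patients whose strategy would have changed. No treatment decision by this panel on FDG material is described, and no repeat decision is planned as a control.

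Study participant eligibility admits "patients deemed resectable and operable at the MDT with or without neoadjuvant chemotherapy".

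**The concern.** To read the proportion as an effect of the tracer, one must assume that the tentative MDT, shown the FDG dossier, would have reached the clinical MDT's decision every time. Nothing in the design tests this. The two decisions differ in tracer, but also in date and setting: one is a live clinical meeting, the other a retrospective research meeting. They may also differ in who attends.

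If a panel does not always reproduce an earlier decision on the same information, the measured proportion is above zero even when FAPI adds nothing. The Discussion says the study was designed to evaluate clinical role and value because earlier reports neglected them, and the abstract names patient management in its primary objective. The figure is therefore likely to be quoted as evidence of clinical impact.

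**Working it through.** **The comparator.** No sentence names it. Secondary objective 1 contrasts treatment under FAPI with treatment under FDG. The tentative MDT decides treatment on FAPI with FDG excluded. The only treatment decision based on FDG anywhere in the article is the clinical MDT's, and the tentative MDT is defined by contrast with it. The clinical decision is therefore the implied comparator.

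**Inputs.**
- n = 50 confirmed ovarian cancers, with at most 60 recruited; about 25 in Group B have a post-NACT decision (Sample size and patients).
- f = true FAPI-caused change = 11%, the figure the Background cites for treatment-naïve patients in an earlier prospective study. This is 0.11 × 50 = 5.5 patients.
- d = the rate at which the decision would differ without a change of tracer. The documents do not give it; 5%, 10% and 15% are assumed.

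The article states no expected rate for this endpoint and no formal sample size calculation, so there is no planned figure to reproduce.

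**Formula.** If the two sources are independent and never cancel, observed change = 1 − (1 − f)(1 − d) = 0.11 + 0.89d. The spurious part among 50 patients is 0.89d × 50.

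| d (assumed) | Observed change | Spurious, of 50 | Spurious relative to 5.5 |
|---|---|---|---|
| 5% | 0.11 + 0.0445 = 15.5% | 2.2 | 40% |
| 10% | 0.11 + 0.0890 = 19.9% | 4.5 | 81% |
| 15% | 0.11 + 0.1335 = 24.4% | 6.7 | 121% |

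The spurious part equals the true part when 0.89d = 0.11, that is at d of about 12.4%.

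**With no FAPI effect (f = 0).** The expected observed change is d itself. The exact binomial chance of a result at least as large as the cited 11% is:

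| d (assumed) | At least 6 of 50 (12%), primary staging | At least 3 of 25 (12%), post-NACT |
|---|---|---|
| 5% | 4% | 13% |
| 10% | 38% | 46% |
| 15% | 78% | 75% |

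At d = 10%, the expected 5 of 50 has an exact 95% confidence interval of 3.3% to 21.8%, which contains 11%.

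**Selection on the first decision.** At primary staging every patient had already been judged resectable and operable. A re-decision towards non-surgical management counts as change. The reverse cannot occur in this cohort. Switches between direct surgery and neoadjuvant chemotherapy can be seen in both directions.

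**The case against.** Several points on the other side have force.

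- **The comparator is inferred, and this is a condensed article.** A fuller protocol could have FDG dossiers presented as well. But the article does not merely leave this open: it says the treatment decision rests purely on FAPI and that FDG results are excluded.
- **Staging.** The same section says that stage as determined at the tentative MDT is compared for both tracers, so an FDG stage may be assigned there. A reader might extend this concern to upstaging and downstaging. The text does not support that, and the staging comparison is left out of the point. Equally, the staging sentence does not supply an FDG treatment decision.
- **Record cut-off.** Limiting the panel to earlier records reduces hindsight and information differences. That safeguard stands, but it does not show how often the panel would differ on identical FDG information.
- **Panel membership.** A reader might infer that different people decide. The article lists roles only, at a single centre, so different membership is possible but not shown.
- **Selection.** A reader might also object to the phrase "in an unselected consecutive cohort". In context it contrasts with the highly selected patients of earlier studies. The resectability criterion is stated openly, the Discussion concedes that not all patients are covered, and restriction to surgical candidates follows from using histopathology as reference. It is loose wording at most. What remains is the one-directional limit on observable change at primary staging, which on its own lowers the proportion.
- **Status.** The trial is exploratory, the endpoint is listed as secondary, and it is labelled hypothetical.

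**Conclusion.** The point holds for treatment strategy. The plan counts any disagreement between two meetings as change caused by FAPI, and without an FDG-based decision by the tentative MDT no later analysis can separate the two.

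The presence of the problem follows from the text; its size does not. The 2.2 to 6.7 spurious changes per 50 rest on an assumed d of 5% to 15%, on a true change equal to the cited 11%, and on independent sources that do not cancel. A reader might infer that the spurious part is as large as the real one. Under these assumptions that is so only when d exceeds about 12%, and it fails at two of the three values shown. Nor is there a target effect against which to judge it, since the article sets none.

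The diagnostic accuracy analysis is unaffected. This is a worthwhile correction to one secondary objective, not a flaw in the trial as a whole.

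**What to change.** Have the same tentative MDT also record a treatment strategy for each case from the FDG dossier, at primary staging and post-NACT. Present the FAPI and FDG dossiers in random order, separated in time, and without the original clinical decision. Define change as the within-panel FAPI-versus-FDG difference. Some within-panel inconsistency will remain in that difference, so report beside it how often the panel's FDG decision departs from the original clinical decision, as the re-decision rate. Name the comparator explicitly.

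State that the primary-staging result applies to patients whom the FDG-informed MDT judged resectable and operable, so that a change from non-surgical management to surgery cannot be observed there.

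The cost is panel time for about 75–85 more dossiers (50–60 at primary staging plus about 25 post-NACT). It needs no new staff, procedure or patient contact, and actual treatment is untouched. Because FAPI is read only after enrolment is complete, and the article describes the trial as still recruiting, this could be arranged before the panel meets.

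Re-presenting only 25 FDG dossiers would be cheaper but can do little more than flag the problem: 2 re-decisions in 25 give an exact 95% confidence interval of 1% to 26%, which cannot distinguish 5% from 15%.

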### Study objectives

#### Primary objectives

The primary objectives are to compare the FAPI PET/CT and FDG PET/CT findings in primary tumors, regional lymph nodes and distant metastases to a histopathological reference standard to the sensitivity, specificity, positive predictive value (PPV), and negative predictive value (NPV) of the PET/CTs, both at primary staging and post-NACT staging (i.e., staging after NACT, prior to interval debulking). This will include a comparison of the cancer stage determined by FAPI PET/CT and conventional imaging (including [^18^F]FDG PET/CT) at primary staging and post-NACT staging [50, 51]. The proportions of patients downstaged, having unchanged stage, and being upstaged according to the added FAPI PET/CT will be determined.

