### Study design

#### Study flow overview

This prospective study will comply with the Standard for Reporting Diagnostic Accuracy (STARD) criteria. Good Clinical Practice (GCP) will be followed to the extent that this is a diagnostic test accuracy trial involving an investigational medicinal product (IMP) [52].

Patients with newly diagnosed biopsy-verified OC *or* highly suspected OC (based on all the information presented at the Gynecological Cancer Multidisciplinary Team Conference (MDT)) with operable and resectable disease will be identified at the MDT. Based on the standard diagnostic workup, which includes [^18^F]FDG PET/CT and a diagnostic contrast enhanced CT (ceCT), and in line with national and international guidelines, patients will either go directly to surgery (Group A) or undergo neoadjuvant chemotherapy prior to surgery (Group B). Patients in both groups (A + B) will undergo FAPI PET/CT prior to treatment and within 1 week of receiving the primary FDG PET/CT (Fig. 1). The additional FAPI PET/CT will not interfere with or delay routine diagnostic workup or treatment, and the results of the FAPI PET/CT will not be available to the patient or the treating physician. Patients in Group B will undergo post-NACT-staging with conventional imaging (including [^18^F]FDG PET/CT) 2–3 weeks after NACT. In addition to conventional imaging, an additional blinded FAPI PET/CT will be performed at post-NACT staging.

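### The FDG-based stage in the upstaged/unchanged/downstaged comparison is attributed to a tentative MDT that is not shown the FDG PET/CT

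*Protocol article*

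**What the plan says.** All references are to the protocol article.

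- **Primary objectives.** The stage comparison is listed here: "This will include a comparison of the cancer stage determined by FAPI PET/CT and conventional imaging", where conventional imaging includes FDG PET/CT. The outcome follows: "The proportions of patients downstaged, having unchanged stage, and being upstaged according to the added FAPI PET/CT will be determined". Both time points are covered, primary staging and staging after neoadjuvant chemotherapy.
- **Staging and impact on patient management, opening.** Study staging is planned for both tracers: "Tentative staging based on FAPI and [^18^F]FDG PET/CT data will be performed". The next sentence names one forum for the stages being compared: "Staging, as determined at the tentative MDT, will be compared for" the two PET/CTs, at both time points. Patients are then classed by the change that FAPI is said to cause.
- **Same section, closing sentence.** The information given to the clinicians at the tentative MDT is set out: "Supplementary imaging results (excluding the FDG PET/CT results), biochemical data, and medical records prior to the staging time point will be available".
- **Study flow overview, text below Fig. 1.** The tentative MDT is retrospective, and "the MDT differs from the clinical MDT, as clinicians will present study-related" FAPI scans in place of the FDG scans.
- **Study flow overview, main text.** The actual treatment route is chosen at the clinical MDT: "Based on the standard diagnostic workup, which includes [^18^F]FDG PET/CT and a diagnostic contrast enhanced CT (ceCT").
- **Diagnostic accuracy.** Each tracer's scans are read under standardized conditions, with the contrast-enhanced CT available to the interpreters.

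**The concern.** Upstaged, unchanged and downstaged are defined by the difference between two stages in the same patient. The difference can be credited to the tracer only if the tracer is the one thing that differs in how the two stages were made. Here the text sends both stages to one panel and withholds from that panel the scan that one of the stages rests on. Whoever runs the analysis must therefore find the FDG-based stage elsewhere, and the article does not say where. The choice determines what the reported proportions mean, and they belong to the primary objective.

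**Working it through.** The document gives no figure to reproduce for this comparison, and under *Sample size and patients* it states that no formal calculation was made. The check is a comparison of passages, followed by one small piece of arithmetic.

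**Step 1. Can the procedure be followed as written?**

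| Question | FAPI-based stage | FDG-based stage |
|---|---|---|
| Is a study stage planned? | Yes | Yes |
| Forum named for the compared stage | Tentative MDT | Tentative MDT |
| Is the scan shown to that forum? | Yes | No; excluded under *Staging and impact on patient management*, and replaced by FAPI under *Study flow overview* |
| Can the forum assign the stage? | Yes | No |

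No second tentative session with FDG is described. The right-hand column fails, so the comparison cannot be produced as stated.

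**Step 2. What could supply the FDG-based stage?**

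- *The clinical MDT.* Its work-up includes FDG PET/CT, and the article repeatedly contrasts it with the tentative MDT. It is the implied fallback, but no sentence says that its stage is the comparator.
- *The standardized FDG read* under *Diagnostic accuracy*. It exists, is made with the contrast-enhanced CT, and has a FAPI counterpart. No sentence links it to the staging comparison.

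**Step 3. What follows from each?**

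- With the clinical MDT, the FDG-based stage is assigned in real time for patient care, and the FAPI-based stage is assigned retrospectively for the study. The observed shift then contains a tracer part and a setting part, and the classification assigns all of it to FAPI.
- With the two reads, both stages can come from the same kind of step, and the tracer is the intended difference.

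**Step 4. Leverage of one patient.** Inputs from *Sample size and patients*: 50 patients with confirmed ovarian cancer, of whom about 25 have neoadjuvant chemotherapy and a second FAPI scan.

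- Primary staging: 1/50 = 0.02, or 2 percentage points per patient reclassified.
- Post-NACT staging: 1/25 = 0.04, or about 4 percentage points per patient reclassified.

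For scale, the *Background* cites upstaging of 14% in treatment-naive patients in one prospective study (0.14 × 50 = 7 patients) and 36% in newly diagnosed patients in one retrospective study (0.36 × 50 = 18 patients).

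**Step 5. A related mismatch.** *Primary objectives* describes FAPI as added. *Secondary objectives*, *Study flow overview* and *Staging and impact on patient management* have it replace FDG or be shown instead of it. These are different contrasts. FDG plus FAPI against FDG is not the same as FAPI against FDG.

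**The case against.** The best defence is that the intended design is evident. A FAPI-informed tentative MDT is set against the FDG-informed clinical MDT, the comparator is named as conventional imaging including FDG, and the panel's file is limited to what existed before the staging time point so as to imitate the clinical meeting. The exclusion of FDG also comes directly after the description of the treatment-strategy exercise and may be meant only for that. The trial is exploratory, the text is a condensed article, and the running of MDT sessions is detail that a full protocol would carry.

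Part of this stands. A reader might infer that the FDG-based stage has no source at all, or that the historical clinical stage is the only one left. The documents do not support either, because the clinical MDT and the standardized FDG read both exist. A reader might also infer that the clinical stage was made by other people with a different file. No passage says that the panels differ in membership, and the file restriction points the other way. Only the difference in timing and purpose is supported.

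The rest does not remove the point. Neither sentence that withholds FDG is limited to treatment strategy: one describes what the attending clinicians have, the other describes that MDT as a whole. The FDG-based stage is also called tentative, which fits a study stage better than a clinical one. And this is a conflict between sentences that are present, so neither condensation nor an unseen full document explains it.

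**Conclusion.** The concern holds in limited form. The article attributes both compared stages to a panel that is denied one of the two scans, so part of the primary objective cannot be executed as written, at either time point. A source for the FDG-based stage is implied but not stated. If that source is the clinical MDT, the reported shift mixes the effect of the tracer with the effect of the setting.

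The size of the mixing cannot be derived from the documents. The per-patient leverage above assumes that the planned 50 and about 25 patients are all evaluable for staging. It would be tempting to say that source-related disagreement is as large as the expected signal, for instance by assuming 5% to 15% discordance (2.5 to 7.5 of 50) and setting it against the 14% benchmark. That is not supported. The range has no basis in the documents, the 36% figure is cited as well, and such disagreements could go in either direction while upstaging and downstaging are reported separately.

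This should be changed. It does not threaten the lesion-level accuracy comparison.

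**What to change.** 1. Under *Staging and impact on patient management*, derive both stages from the standardized reads described under *Diagnostic accuracy*, each tracer with the same contrast-enhanced CT. Use one FIGO/TNM mapping applied identically to both, and base the three classes on those two stages. Remove the attribution of the compared stages to the tentative MDT.
2. Keep the FAPI-only tentative MDT for treatment strategy. If its stage is also compared with the clinical MDT stage, name that source and report the result as a supportive comparison that mixes tracer and setting.
3. Use one description of the contrast throughout. Align the term *added* under *Primary objectives* with the replacement wording in the other sections.

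**Cost.** A change of wording and one mapping table. No patient procedure changes. FAPI scans are interpreted only after all patients are enrolled, so the rule can be fixed before any FAPI result is known. The downside is that a read-based stage does not use the biochemistry and records open to the MDT, since the readers are blinded to clinical information other than the cancer diagnosis. The supportive comparison in item 2 keeps that view available.
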